### **2.2 FORMULATION AND MANUFACTURING OF AGRIFLU (TIV)**

Study sites will refer to the AGRIFLU package insert for complete product information regarding the TIV used in this study. AGRIFLU is manufactured by Novartis, and each 0.5 mL

single dose of AGRIFLU contains 45 mcg total comprised of 15 mcg of influenza virus hemagglutinin of 3 different influenza strains used for the current influenza season. The TIV used for the booster injection at Week 16 in Group 2 and for the prime in Group 4 and Group 6 will be a licensed Northern Hemisphere (NH) product approved by the U.S. FDA for administration in the 2012/13 influenza season and composed of three influenza strains: A/California/7/2009 (H1N1)pdm09-like, A/Victoria/361/2011 (H3N2)-like and B/Wisconsin/1/2010-like). The TIV used for the last study injection in Group 4 and Group 6 will be a licensed NH product approved by the U.S. FDA for administration during the 2013-14 influenza season. The composition of 2013/14 TIV will be determined in February 2013 with availability estimated to be August 2013.

### **2.3 FORMULATION AND MANUFACTURING OF FLUAD (ATIV)**

Study sites will refer to the FLUAD Investigators Brochure for complete product information regarding the ATIV used in this study. FLUAD is manufactured by Novartis and is studied as an investigational product in U.S. under the Investigational New Drug (IND) application with FDA. Each 0.5 mL single dose of FLUAD contains 45 mcg total comprised of 15 mcg of influenza virus hemagglutinin of 3 different influenza strains used for the current influenza season formulated with proprietary MF59 adjuvant in a pre-filled syringe. The ATIV used for the booster injection at Week 16 in Group 1 and for the prime injection in Group 3 and Group 5 will include the same strains as NH product approved by the U.S. FDA for administration in the 2012/13 influenza season, composed of three influenza strains: A/California/7/2009 (H1N1)pdm09-like, A/Victoria/361/2011 (H3N2)-like and B/Wisconsin/1/2010-like). The ATIV used for the last study injection in Group 3 and Group 5 will include the strains approved by the U.S. FDA for administration for the 2013-14 influenza season. As with the TIV, the composition of the 2013-2014 ATIV will be determined in February 2013 with availability estimated to be August 2013.

### **2.4 PRE-CLINICAL STUDIES OF HA DNA VACCINES**

No preclinical pharmacology, toxicology, pharmacokinetic, or metabolism studies were conducted for the seasonal influenza DNA vaccine VRC-FLUDNA063-00-VP. There is extensive clinical experience with licensed seasonal influenza products, including the antigens present in the 2011/12 seasonal influenza vaccine, as well as human clinical trial experience with DNA vaccines constructed using the same plasmid backbone and CMV/R promoter, including other seasonal influenza DNA vaccines.

FDA recommendations permit manufacturers with established seasonal flu vaccines to file supplemental applications each year after changing one or more of the three influenza strains in the vaccine. This reflects the large safety experience with similar influenza vaccine products as well as the severe time constraints on design and manufacture of both investigational and licensed vaccines due to the seasonality of influenza infections. Although VRC is evaluating investigational vaccines based on the DNA platform, the influenza gene inserts mimic the antigens found in the yearly seasonal TIV and our approach has been similar in this regard.

Refer to the Investigator's Brochure for more information about preclinical studies.

### 3 STUDY OBJECTIVES

For the study objectives, an HAI response (seroconversion) is defined as  $\geq 1:40$  for baseline-negative subjects or 4-fold greater than baseline for subjects with pre-existing immunity.

#### 3.1 PRIMARY OBJECTIVES:

- To evaluate the safety and tolerability of each vaccination schedule
- To evaluate the safety and tolerability of concurrent administration of the HA DNA vaccine and either ATIV (FLUAD) or TIV (AGRIFLU) administered in different arms on the same day
- To compare the frequency and magnitude of the 2012/13 influenza vaccine strain-specific HAI response at 3 weeks after the ATIV boost in Group 1 to 3 weeks after the ATIV prime in Group 3, as well as to compare the same responses at 3 weeks after the TIV boost in Group 2 to 3 weeks after the TIV prime in Group 4.

#### 3.2 SECONDARY OBJECTIVES:

- To evaluate the frequency and magnitude of strain-specific HAI responses at 3 weeks after each study injection for all Groups for the 2012/13 and 2013/14 influenza vaccine strains.
- To evaluate the frequency and magnitude of 2012/13 and 2013/14 influenza vaccine strain-specific H1, H3 and B neutralizing antibodies that are 4-fold greater than baseline at 3 weeks after each study injection for all Groups.
- To compare the frequency and magnitude of the 2012/13 influenza vaccine strain-specific HAI responses at 3 weeks after each ATIV injection in Groups 1, 3, and 5 to the HAI responses after the respective TIV injections in Groups 2, 4, and 6.

#### 3.3 EXPLORATORY OBJECTIVES:

- To evaluate the presence of anti-stem antibodies pre- and post-vaccination for all Groups.
- To evaluate the magnitude, frequency, breadth and quality of antibody or T cell responses for all Groups over the time course of the study.

### 4 STUDY DESIGN

This is a Phase 1b, randomized study in healthy adults to assess the safety, tolerability, and immunogenicity of same season and sequential season vaccination schedules as shown in **Table 4-1** below. The hypotheses are: the HA DNA vaccine will be safe for human administration; the schedules that include an HA DNA vaccination will elicit a higher titer antibody response than the schedules with TIV or ATIV only; and the response will have broader neutralizing activity against antigenically diverse influenza strains.

The schema shown projects the starting month for Groups 1 and 2 as August 2012, and the Boost month for Groups 3, 4, 5 and 6 as August 2013. This projected timing is premised on the

experience that in recent years, supplies of inactivated vaccine have become available for shipping to sites in late July to early August. As there may be delay in product manufacturing for various reasons, if the TIV and/or ATIV products are not available for administration in August, the timeframe will be shifted to be based on availability of both products. A notice will be distributed to sites to address any issues related to scheduling visits for administration of vaccinations and to keep the intervals comparable between the groups that will receive TIV and groups that will receive ATIV.

**Table 4-1. Study schema**

| Group | Subjects | Stratification
by age                                                                                                                                                                                                                                  | Prime -*Aug 2012
Day 0 | Boost-Nov 2012
Week 16             |                            |
|-------|----------|-----------------------------------------------------------------------------------------------------------------------------------------------------------------------------------------------------------------------------------------------------------|---------------------------|---------------------------------------|----------------------------|
|       |          |                                                                                                                                                                                                                                                           | 2012/13 strains           |                                       | 2013/14 strains            |
| 1     | 55       | 1a: 18-50 years                                                                                                                                                                                                                                           | HA DNA                    | ATIV                                  | -                          |
|       |          | 1b: 51-70 years                                                                                                                                                                                                                                           |                           |                                       |                            |
| 2     | 55       | 2a: 18-50 years                                                                                                                                                                                                                                           | HA DNA                    | TIV                                   | -                          |
|       |          | 2b: 51-70 years                                                                                                                                                                                                                                           |                           |                                       |                            |
| Group | Subjects | Stratification
by age                                                                                                                                                                                                                                  |                           | Prime-Oct/Nov 2012
Day 0           | Boost-*Aug 2013
Week 44 |
| 3     | 55       | 3a: 18-50 years                                                                                                                                                                                                                                           |                           | ATIV                                  | ATIV                       |
|       |          | 3b: 51-70 years                                                                                                                                                                                                                                           |                           |                                       |                            |
| 4     | 55       | 4a: 18-50 years                                                                                                                                                                                                                                           |                           | TIV                                   | TIV                        |
|       |          | 4b: 51-70 years                                                                                                                                                                                                                                           |                           |                                       |                            |
| 5     | 55       | 5a: 18-50 years                                                                                                                                                                                                                                           |                           | HA DNA (left arm)
ATIV (right arm) | ATIV                       |
|       |          | 5b: 51-70 years                                                                                                                                                                                                                                           |                           |                                       |                            |
| 6     | 55       | 6a: 18-50 years                                                                                                                                                                                                                                           |                           | HA DNA (left arm)
TIV (right arm)  | TIV                        |
|       |          | 6b: 51-70 years                                                                                                                                                                                                                                           |                           |                                       |                            |
| Total | 330      | * May be delayed pending TIV/ATIV availability.
All vaccinations are open-label and intramuscular (IM) in the deltoid.
HA DNA injections will be administered via Biojector.
ATIV and TIV injections will be administered by needle and syringe. |                           |                                       |                            |

The expected duration of time on study per subject is approximately 40 weeks for Groups 1-2 and 64 weeks for Groups 3-6.

#### 4.1 STUDY POPULATION

The study is designed for healthy adults ages 18-70 years. The enrollment will be stratified by age groups to have an equal representation of healthy younger (18-50 years) and older (51-70 years) adults in the comparison groups.

The following eligibility criteria will be used:

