|       |          | 5b: 51-70 years                                                                                                                                                                                                                                           |                           |                                       |                            |
| 6     | 55       | 6a: 18-50 years                                                                                                                                                                                                                                           |                           | HA DNA (left arm)
TIV (right arm)  | TIV                        |
|       |          | 6b: 51-70 years                                                                                                                                                                                                                                           |                           |                                       |                            |
| Total | 330      | * May be delayed pending TIV/ATIV availability.
All vaccinations are open-label and intramuscular (IM) in the deltoid.
HA DNA injections will be administered via Biojector.
ATIV and TIV injections will be administered by needle and syringe. |                           |                                       |                            |

The randomization to Groups 1 and 2 will occur first. Once these groups are filled, randomization to Groups 3-6 will occur. Randomizations are stratified by age, subgroups “a” includes subjects 18-50 years of age and subgroups “b” includes subjects 51-70 years of age, in order to keep similar age distribution to the groups.

**Study Duration:** Subjects will be evaluated for safety and immune responses throughout the trial for 24 weeks following the boost. Duration of time on study will be 40 weeks for Groups 1 and 2 and 68 weeks for Groups 3, 4, 5 and 6.

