## 6.4 **SAMPLE SIZE AND ACCRUAL**

The study is planned to enroll a total of 330 healthy adults stratified by age groups (18-50 and 51-70) to receive one of six vaccine regimens defined in **Table 4-1**. The first 110 subjects enrolled will be randomized with equal allocation to receive 2012/13 HA DNA prime with 2012/13 ATIV boost (Group 1) or 2012/13 HA DNA prime with 2012/13 TIV boost (Group 2). The remaining 220 subjects will be randomized with equal allocation to receive 2012/13 ATIV

with 2013/14 ATIV boost (Group 3), 2012/13 TIV with 2013/14 TIV boost (Group 4), concurrent administration of 2012/13 HA DNA and ATIV with 2013/14 ATIV boost (Group 5), or concurrent administration of 2012/13 HA DNA and TIV with 2013/14 TIV boost (Group 6).

Enrollments may occur rapidly at more than one site. The EMMES Corporation will carefully monitor study enrollment and notify all sites and the VRC Protocol Chair when the completion of enrollment is near in order to end recruitment and to plan how to fairly accommodate, to the degree possible, the enrollment of eligible volunteers that have already been recruited. The decision to stop study enrollments will be made by the VRC Protocol Chair.

This study is not designed to test a formal null hypothesis for superiority or non-inferiority. This section does provide an indication of the power available to observe specific events (e.g., particular adverse events) assuming a range of underlying “true” rates, the precision available in estimating immune response rates, and the power to detect differences in response rates between Study Groups. While drop-out is expected to be low, power calculations assuming approximately 10% drop-out (N=50/per group) are also presented.

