#### 6.5.4 Analysis of Immune Responses

The primary analysis for immunogenicity will employ the intent-to-treat (ITT) principle, i.e., all data from enrolled subjects will be used, and subjects will be analyzed according to the study regimen to which they were randomized regardless of the product(s) received. If there are cases of a subject receiving a regimen different from the randomized assignment or subjects who did not complete the prime-boost regimen, then per-protocol analysis may also be performed, according to actual study product received and excluding subjects who did not complete the prime-boost regimen.

The frequency of immune response will be analyzed by tabulating the seroconversion (proportion of subjects with either a pre-vaccination strain-specific HAI titer  $<1:10$  and a post-vaccination HAI titer  $\geq 1:40$  or a pre-vaccination HAI titer  $\geq 1:40$  and a minimum four-fold rise in post-vaccination HAI antibody titer) and exact 95% confidence intervals for each study group. The magnitude of immune response will be analyzed by tabulating the geometric mean titer for each study group. The immune response may also be summarized separately for each age

subgroup. Fisher's exact tests will be used to compare seroconversion between any two study groups.

Missing responses will be assumed to be missing at random, i.e., conditional on the observed data the missingness is independent of the unobserved responses, no imputations for missing data will be made.

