#### 6.5.6 Randomization of Treatment Assignments

Enrollment and randomization into Group 1 and Group 2 are targeted to begin in August 2012, enrollment and randomization into Groups 3, 4, 5 and 6 are targeted to begin in October 2012. Enrollment and randomizations will be done online using the enrollment module of The EMMES Corporation's Internet Data Entry System (IDES). The randomization code will be prepared by statisticians at The EMMES Corporation and included in the enrollment module for the trial. To decrease the potential for subject dropouts during the period between randomization and initial vaccination, the electronic data system will assign each subject a randomized study group assignment after the eligibility to begin Day 0 study injections has been entered into the system.

The first 110 subjects enrolled will be randomized with equal allocation to Group 1 or Group 2. The subsequent 220 subjects enrolled will be randomized with equal allocation to Group 3 – Group 6. Randomization will be stratified by clinical site and age (18-50 or 51-70). Manual back-up procedures and instructions will be provided for use in the event that the site temporarily loses access to the Internet or the online enrollment system is unavailable to a study site.

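### The age balance described in section 4.1 has no stratum target behind it, and age stratification within two sequential waves does not secure it for the primary comparisons (Group 1 vs 3, Group 2 vs 4)

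*Protocol*

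**What the plan says.** Three places in the protocol describe the purpose or use of age stratification.

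- Section 4.1: enrolment is stratified by age with the aim of "equal representation of healthy younger (18-50 years) and older (51-70 years) adults in the comparison groups".
- Précis: the randomisations are stratified by age "in order to keep similar age distribution to the groups". This is a weaker aim than equal numbers.
- Section 6.5.4: "The immune response may also be summarized separately for each age" subgroup. The age summary is optional.

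The mechanism is in sections 6.4 and 6.5.6.

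- Section 6.4: "The study is planned to enroll a total of 330 healthy adults stratified by age groups (18-50 and 51-70"). No number per age band follows.
- Section 6.5.6: "The first 110 subjects enrolled will be randomized with equal allocation to Group 1 or Group 2", then "The subsequent 220 subjects enrolled will be randomized with equal allocation to Group 3" through Group 6.
- Section 6.5.6: "Randomization will be stratified by clinical site and age (18-50 or 51-70").

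Table 4-1 lists an a and a b subgroup in every group but prints only the group total of 55. The précis says Groups 1 and 2 are filled before Groups 3-6 open. Section 6.5.6 targets August 2012 for the first wave and October 2012 for the second. Sections 3.1 and 6.4.3 make Group 1 vs 3 and Group 2 vs 4 the primary immunogenicity comparisons, and section 6.5.4 compares seroconversion by Fisher's exact test.

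**The concern.** Stratified randomisation shares out whoever enrols evenly among the arms of one randomisation. It does not decide how many people of each age enrol. Two things follow.

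First, nothing in the protocol fixes the size of the older band, so a half-and-half split is left to recruitment. Second, stratification balances age between Groups 1 and 2, and among Groups 3 to 6, but not between the waves. Both primary comparisons take one group from each wave. If the first wave closes with a different age mix from the second, the compared groups differ in age, and the planned test does not take account of it.

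The protocol itself gives reason to think age matters. Section 1.1 reports lower efficacy of inactivated vaccine at older ages, and section 1.2 mentions older adults as a population that DNA priming might serve. At stake is whether a difference of a few points between Group 1 and Group 3, or between Group 2 and Group 4, can be read as an effect of priming.

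**Working it through.** **1. The plan's own figure.** The inputs from Table 6-3 are seroconversion 0.4 vs 0.7, Fisher's exact test and 5% type I error. Summing over all pairs of binomial outcomes (two-sided) gives 84.6% power at N=55 and 82.9% at N=50. The table states 85% and 83%, so it is reproduced. The inputs are overall group rates, and stratum size does not enter. The stated power therefore does not depend on the age split.

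**2. What the allocation secures.**

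| Comparison | Same randomisation? | Age balanced by stratification? |
|---|---|---|
| 1 vs 2 | yes | yes |
| Among 3, 4, 5, 6 | yes | yes |
| 1 vs 3 (primary) | no | no |
| 2 vs 4 (primary) | no | no |

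A 50:50 split within a group is not secured in any row.

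**3. Size of the cross-wave shift.** Let s be the older share and p_y, p_o the seroconversion rates in younger and older subjects. With no vaccine effect, the group rate is p_y(1 − s) + p_o·s. The difference between waves is then

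(s₂ − s₁) × (p_y − p_o).

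The protocol gives neither shares nor rates by age, so these are assumptions. With waves 70% and 50% younger, s₂ − s₁ = 0.20:

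- age gap 0.10: 0.20 × 0.10 = 0.02
- age gap 0.20: 0.20 × 0.20 = 0.04
- age gap 0.30: 0.20 × 0.30 = 0.06

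Over share differences of 0.1-0.4 and age gaps of 0.1-0.3, the shift runs from 0.01 to 0.12. Table 6-4 gives minimum detectable differences of 0.18-0.29.

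**4. Effect on the unstratified Fisher test.** Take a younger rate of 0.7 (assumed), N=55 per group and no vaccine effect. Group counts are treated as binomial at the averaged rate.

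| Older shares | Age gap | Expected rates | Rejection rate |
|---|---|---|---|
| 50% and 50% | 0.30 | 0.55 vs 0.55 | 2.8% |
| 30% and 50% | 0.10 | 0.67 vs 0.65 | 3.6% |
| 30% and 50% | 0.20 | 0.64 vs 0.60 | 4.7% |
| 30% and 50% | 0.30 | 0.61 vs 0.55 | 6.3% |
| 20% and 50% | 0.30 | 0.64 vs 0.55 | 11% |

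Holding the age counts fixed (16 or 17 older in one group, 27 or 28 in the other) gives slightly lower values for the 30% and 50% rows: about 3.5% at a gap of 0.10, and 4.8-6.0% at 0.30.

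**5. Precision within the older band.** Exact 95% intervals near an observed 50%:

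- equal strata, 14/27: 0.32-0.71, width 0.39
- 30% older (0.30 × 55 ≈ 16), 8/16: 0.25-0.75, width 0.51
- 20% older (0.20 × 55 = 11), 6/11: 0.23-0.83, width 0.60

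Within-stratum Fisher power for 0.4 vs 0.7 is 48% at 27 per group, 51% at 28, 27% at 16 and 16% at 11. Even equal strata would not support an age-specific comparison of that size.

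**The case against.** The best defence is that section 4.1 can be read as meaning that each age band is represented equally across the groups being compared, not that each group is half older. The précis supports this reading. On it, the plan delivers what it says for 1 vs 2 and among Groups 3-6. That stands, and it removes any flat claim that the protocol promises 50:50 and breaks the promise. It does not cover 1 vs 3 and 2 vs 4, which are the primary comparisons.

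A reader might also infer that the trial is failing older adults because their stratum could be too small to analyse. The documents do not support making this the main harm. Age appears in no objective or endpoint, the age summary is optional, and equal strata would still give only 27-28 per group.

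A reader might further infer that the primary tests have a badly inflated error rate. The 11% figure needs a 30-point age gap together with a 30-point difference in older share, and the protocol gives no evidence for either. Section 6.4 also says the study is not designed around a formal superiority or non-inferiority hypothesis.

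Two more points stand. Enrolment itself is described as age-stratified and runs through a monitored electronic module, so a target could have been set there, but the protocol states none and points to no document that does. And age is only one way in which two waves may differ, so balancing it leaves the rest of the non-concurrent comparison as it is.

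**Conclusion.** The point holds in a limited form. The property described in section 4.1 is not secured in any group on the half-and-half reading. On the milder reading it is not secured for the two primary comparisons, because age is stratified only within each wave and the test named in section 6.5.4 is unstratified.

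The plausible effect is a shift of 2-6 points in group seroconversion rates. This rests on assumed mixes of 70% vs 50% younger and assumed age gaps of 10-30 points. Under those mixes and a younger rate of 0.7, the Fisher test's false-positive rate stays near its nominal level (about 3.5% to 6.3%). Table 6-3 is unaffected.

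Severity is minor to moderate. It merits action because the aim is the sponsor's own and an enrolment target has to act before subjects enter. An analysis plan could adjust for age afterwards, but it could not restore a mix that was never enrolled.

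**What to change.** In sections 4.1, 6.4 and 6.5.6, set the same age-stratum target for both waves and apply it in the enrolment module: about 55 younger and 55 older for Groups 1-2, and about 110 and 110 for Groups 3-6. Print the targets in Table 4-1. Because 55 is odd, this means 27 or 28 per age band in each group.

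Rigid closure at 50:50 is stricter than needed. Groups 3-6 are primed in October/November and limited to 20 enrolments a week for the first two weeks (section 4.3). If a stratum cannot fill within the vaccination window, hold Groups 3-6 to the age proportion actually reached in Groups 1-2. That still gives the primary comparisons matching age mixes.

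If no target is wanted, reword section 4.1 to match the précis and stratify the 1 vs 3 and 2 vs 4 comparisons by age band.

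The cost is a module setting and a few lines of text. The downside is possibly slower accrual in one age band, which matters most for Groups 3-6. The rewording option costs almost nothing at enrolment but leaves the age mix to recruitment. None of these changes removes other differences between the two waves.
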